### Demographics

AGYW and MF will report their age, education, employment, income, food and housing security, marital status, and number of children. AGYW who report being married at baseline will be excluded.

### Primary outcome

AGYW uptake of HIV testing at 6-months post-intervention.

### Secondary outcomes

AGYW uptake of HIV testing at 12-, 18-, and 24-months. At 6-, 12-, 18-, and 24-months, AGYW PrEP uptake; HIV and STI incidence (gonorrhea, chlamydia, and trichomoniasis); Self-reported sexual behavior (e.g., condom use, substance use during sex, number of partners, concurrent partners) [48]. Standard cost evaluation methods [49, 50], including personnel time and non-personnel resources (e.g., travel expenses, snacks, incentives, curricular materials).

**Mediators and moderators**: At baseline, 6-, 12-, 18-, and 24-month follow-up: AGYW and MF reported HIV and STI knowledge [51], and PrEP knowledge and attitudes [52], parental acceptance and rejection in the AGYW-MF relationship [53], and quality and quantity of AGYW-MF communication [54–56]. AGYW will indicate their mental health and trauma exposure [57–60], substance use [61–63], and partner dynamics and communication [56, 64, 65].

**Sample size.** The sample size (*N* = 600–650 AGYW-MF dyads; *N* = 1,200–1,300 participants) was determined based on the primary hypothesis that HIV testing at 6-months will be higher among AGYW who receive ZAIMARA versus HP. Assuming 10% attrition at 6-months, we will have a sample size of *n* = 270 AGYW in ZAIMARA and *n* = 270 AGYW in HP. With at least 80% power, a 2-tailed significance level of 0.05, and the assumption of proportions in ZAIMARA and HP of 0.454 (null hypothesis), we will be able to detect a difference of 0.12 between the group proportions (equivalent to risk ratio = 1.26).

Effect sizes for binary outcomes is given in terms of the relative risk (RR), where RR = 1 indicates no treatment effect. A RR < 1 indicates a protective effect of the intervention. With 80% retention, we will have ≥ 80% power to detect RRs ≤ 0.38 when the proportion in the control group is 20%, and RRs ≤ 0.65 when the proportion in the control group is 50%. We calculated the standard effect size (*d*) in standard deviations for group mean comparisons with 80% power for continuous outcomes, where *d* = 0 is defined as no treatment effect. We will be able to detect a small to medium effect size (*d* = 0.36) even with 75% retention. Low HIV incidence among AGYW (2.54%) per year will allow us to explore incidence, but we do not expect sufficient statistical power to test intervention effects on HIV incidence.

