**Randomization**. We will randomize AGYW-MF dyads to one of two conditions (ZAIMARA or HP) following the baseline assessment (Fig. 1). We will use stratified permuted block randomization (blocks of 2) to ensure uniform distribution across arms and a balanced allocation (*n* = 300–325 ZAIMARA and *n* = 300–325 HP) throughout enrolment. AGYW and MF dyads will be randomized to the same condition. By stratifying the randomization process at the clinic level, we will account for potential variations in participant characteristics by neighborhood or clinic-specific factors, enhancing the validity and reliability of the study findings. Pre-determined randomization logs at each site will guide assignment to arms.

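### The detectable effects printed for secondary outcomes (RR 0.38, RR 0.65, d = 0.36) fit about 120 AGYW per arm, roughly half of what the stated sample and retention give

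*Protocol article*

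**What the plan says.** The Randomization paragraph of Aim 2 allocates dyads 1:1, with "300–325 ZAIMARA" and the same number in health promotion.

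The Sample size paragraph (printed under Secondary outcomes, Aim 2) first covers the primary outcome. It uses 270 AGYW per arm after 10% attrition, "a 2-tailed significance level of 0.05", at least 80% power, and a detectable difference of 0.12 from 0.454.

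It then turns to the other outcomes. For binary outcomes at 80% retention, it claims at least 80% "power to detect RRs ≤ 0.38 when the proportion in the control group is 20" per cent, with RR 0.65 given for a control proportion of 50%. For continuous outcomes: "We will be able to detect a small to medium effect size", put at d = 0.36 and said to hold at 75% retention. It notes that "RR < 1 indicates a protective effect of the intervention".

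No intracluster correlation, design effect, adjusted alpha or analysis subset is given for these three figures. The Statistical analysis section foresees random intercepts for clustering only if they prove necessary.

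**The concern.** The retained sample follows directly from numbers the article prints, and the three effects look too large for it. With 240 per arm, a trial should detect a good deal less than a fall from 20% to 7.6%, which is what RR 0.38 means.

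Two things are at stake. First, the sentences read as limits of detectability. A funder or monitoring board would take them to mean that a halving of a 20% STI proportion lies beyond the trial's reach, and STI outcomes also feed the cost-effectiveness analysis. Secondly, if the figures contain an undisclosed allowance for clustering, the two halves of one paragraph rest on different assumptions, and the reader cannot tell which is meant.

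**Working it through.** **Inputs.** 300 to 325 randomised per arm (Randomization, Aim 2). Retention is 80% for binary and 75% for continuous outcomes (Sample size paragraph). Two-sided alpha 0.05 is stated for the primary outcome and assumed here for the secondary ones. Power is 80%. Then (1.960 + 0.8416)² = 7.849.

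Retained per arm:
- 80%: 0.80 × 300 = 240; 0.80 × 325 = 260.
- 75%: 0.75 × 300 = 225; 0.75 × 325 = 244.

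**1. Reproduce the primary figure.** With n = 7.849 × (p₁q₁ + p₂q₂)/(p₁ − p₂)², 0.454 against 0.574 gives 7.849 × (0.2479 + 0.2445)/0.0144 = 268.4, so 269 per arm. The pooled-variance version gives 272. Power at 270 per arm is 80.2% unpooled and 79.8% pooled, and 0.574/0.454 = 1.26. The primary statement reproduces with no design effect.

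**2. Back-solve the secondary figures with the same formula.**
- RR 0.38 at 20% (0.20 v 0.076): 7.849 × (0.1600 + 0.0702)/0.124² = 117.5 per arm; pooled 120.3.
- RR 0.65 at 50% (0.50 v 0.325): 7.849 × (0.2500 + 0.2194)/0.175² = 120.3; pooled 123.0.
- d = 0.36: 2 × 7.849/0.36² = 121.1.

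Three separate figures agree on about 120 per arm: 120/240 = 50% of the retained sample for the RRs, and 121/225 = 54% for d. In the other direction, 120 per arm gives RR 0.379 to 0.385, RR 0.646 to 0.650 and d = 0.362.

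**3. Can another method explain it?** Required n per arm for the printed effects:

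| Variant | RR 0.38 | RR 0.65 | d = 0.36 |
|---|---|---|---|
| Continuity-corrected | 136 | 135 | – |
| Log-RR | 136 | 131 | – |
| Arcsine | 116 | 123 | – |
| One-sided 0.05 | 95 | 97 | 96 |
| 90% power | 161 | 165 | 163 |
| Alpha 0.01 | 180 | 184 | 181 |

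None reaches 225 to 240.

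**4. Power for the printed effects at the stated n (pooled for the RRs).** RR 0.38 at 240 per arm: 97.8%. RR 0.65 at 240: 97.5%. d = 0.36 at 225: 96.8%.

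**5. Minimum detectable effects at the stated n, 80% power.**

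| Outcome | n per arm | Printed | Recomputed |
|---|---|---|---|
| Control 20% | 240 | RR 0.38 | RR 0.540 pooled, 0.542 unpooled |
| Control 50% | 240 | RR 0.65 | RR 0.747 pooled, 0.748 unpooled |
| Continuous | 225 | d = 0.36 | 2.8016 × √(2/225) = 0.264 |

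At the upper enrolment, 260 per arm gives RR 0.56 and 0.76, and 244 per arm gives d = 0.254. The gap is then slightly wider.

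Rounding matters when these are restated. At 240 per arm, RR 0.75 has 79.5% power (unpooled), and d = 0.26 at 225 has 78.7%. The values 0.74 and 0.27 keep power above 80%.

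**The case against.** The best defence is that the statements are literally true. The binary claim is for at least 80% power, and actual power is about 98%. The continuous claim, read as a capability, also holds. That stands: a reader who inferred that the trial is underpowered for these effects would be mistaken. The sample size rests on the primary hypothesis alone, so no design decision depends on the three figures. Nor does the article say that only very large reductions can be found, and a null result will be read from its estimate and interval.

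A second defence is that 240 independent, evaluable outcomes per arm is optimistic. AGYW may decline STI testing and stay in the study, may not be sexually active, and attend workshops in groups of about 6 to 10. This also stands, as a caution on the recomputed limits: they are best cases at 300 per arm. It does not rescue the printed figures, because no such allowance is stated. Restricting to the 63% or so who report sexual activity in the Background would leave about 0.63 × 240 = 151 per arm, still not 120.

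A design effect of about 1.8 to 2.0 would produce the figures. It is tempting to conclude that the primary outcome then has only about 51% power (270/2 = 135 effective per arm, 0.454 v 0.574). The document does not support this: no design effect is given anywhere, so that figure is conditional and shows no error in the primary calculation. Another possible explanation, also only an inference, is that the per-arm count was used as the total (240/2 = 120).

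Finally, a reader might object that effects are given only for RR below 1, although PrEP uptake and later HIV testing are secondary outcomes where benefit means RR above 1. This is minor. The protective convention is normal for STI and risk behaviour, and the primary statement already gives an uptake effect of 1.26.

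**Conclusion.** The inconsistency is real and follows from the article's own numbers. RR 0.38, RR 0.65 and d = 0.36 belong to about 120 AGYW per arm, against 240 (80% of 300) and 225 (75% of 300). They are wrong as minimum detectable effects and do not share a basis with the primary calculation beside them.

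The error is conservative: it understates what the trial can detect. At a 20% control proportion, the printed limit is a 62% relative reduction, whereas the stated n supports about 46%. The primary sample size is unaffected. Severity is moderate.

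The conclusion assumes that the two-sided 0.05 level applies to secondary outcomes. The recomputed limits further assume that each retained AGYW contributes an independent, evaluable outcome.

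**What to change.** Restate the paragraph along these lines: assuming independent, evaluable outcomes, 80% retention (240 per arm) gives 80% power for an RR of about 0.54 at a 20% control proportion and about 0.747 at 50% (0.74 if rounded conservatively); 75% retention (225 per arm) gives a d of about 0.264 (0.27 if rounded conservatively). Optionally, for uptake outcomes, add an RR of about 1.56 at 20% and about 1.26 at 50%, both rounded conservatively.

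If the printed figures instead assumed a design effect or an evaluable subset of about half the sample, keep them and state that assumption. If it was a design effect for group delivery, apply the same one to the primary power statement.

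The cost is three recalculated numbers and an edit to one paragraph. Enrolment, the primary analysis and trial conduct do not change, unless a design effect is disclosed, in which case the primary power statement must be reworked too.

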### Aim 3 impact of monthly mental health screening with referral on peer leader job retention

**Overview.** Peer leaders will be individually randomized within site and arm (ZAIMARA vs. HP) to receive a monthly mental health screening plus referral for services where relevant versus monthly nutrition and exercise screening with instructions for improvement where relevant. We will compare job retention at 6-months (primary outcome) and job satisfaction at 6- and 12-months.

**Participants**. All peer leaders (approximately *N* = 60 plus any new hires during the study) will be eligible to participate.

**Recruitment.** We will invite all peer leaders to participate in the study prior to training. The study coordinator will contact each peer leader, explain the study, and request participation. All peer leaders will be employed and paid by the study for non-research activities.

**Consent**. Peer leaders who express interest in participating in the study will engage in formal consent procedures by research assistants prior to the baseline assessment. Peer leaders who do not want to participate in the research will be trained to deliver the intervention and participate in supervision but will not contribute study data.

**Retention.** At baseline, we will obtain peer leaders’ phone numbers, home addresses (and draw a map), and other contact information (phone/text/WhatsApp). We will also collect the phone numbers, home addresses, and text/WhatsApp information for at least one other person who will always know how to reach them in the future. At least one month before each follow-up assessment, we will contact peer leaders to confirm the appointment. We will attempt to retain all peer leaders even if they resign from their employment with the study. If we do not reach the peer leader after one week and at least three attempts, we will follow several steps: 1) If the phone number/text/WhatsApp is disconnected, we will contact people from peer leaders’ records; (2) If peer leaders were recruited through any other projects, we will seek their assistance to locate them; (3) Research assistants will visit peer leaders’ last known address to try to locate them in-person. (4) If peer leaders no longer live at the address, we will ask their contacts to help us locate them.

**Randomization.** We will randomize peer leaders to one of two conditions, mental health distress screening with referral (*n* = 30) or nutrition and exercise screening with improvement suggestions (*n* = 30) prior to the first workshop at the site but after the baseline assessment (Fig. 2). We will stratify peer leader randomization by treatment arm (ZAIMARA and HP) and age (22–29 years-old or ≥ 30 years-old) using predetermined block size.

**Fig. 2 Fig2:**
[figure not shown]
Flowchart for Peer Leader Mental Health Distress Screening versus Nutrition and Exercise Screening

**Monthly health screening procedures.** During the 4th supervision session each month, peer leaders will complete a standard screening of their mental health distress or nutrition and exercise on a handheld computer tablet. The weekly supervision session and the screening will be conducted separately. Peer leaders whose mental health screen indicates distress will receive a prompt with a referral for additional evaluation by a mental health professional. Peer leaders who report sub-optimal nutrition and exercise will receive a notification immediately following their screening with instructions for improvement (see below). The study nurse will collect the tablets and document peer leader scores and referrals.

**Screening measures**. Peer leaders randomized to the mental health distress screening and referral condition will complete the *Kessler Psychological Distress Scale*−5 (*K5*), a 5-item self-report measure of psychological distress over the past four weeks [66]. Peer leaders who screen positive for mental health distress (≥ 11) will receive a prompt with a referral for additional evaluation and support by a mental health professional. Peer leaders randomized to nutrition and exercise will complete two sections about nutrition and physical activity on the *Fantastic Lifestyle Checklist* [67]. Peer leaders who report sub-optimal nutrition and exercise (≤ 13 on *Fantastic Lifestyle Checklist*) will receive a prompt to examine areas where they scored 0 and 1 and choose one area to change. Once they make their selection, they will receive tips on how to change, including seeking advice from the health care clinic or a personal trainer.

**Exit interviews.** If a peer leader resigns, we will conduct an exit interview to understand their reasons for leaving. Interviews will be conducted by a trained research assistant addressing themes associated with job satisfaction, self-efficacy, support, and workplace stress. This will inform future peer leader-led interventions.

**Study assessments**. Peer leaders will complete a ~ 40-minute baseline survey via CASI pre-training, pre-workshop day, and 6-, and 12-months after the first workshop. They will receive K200 (~$9.00) at the end of each assessment plus K200 (~$9.00) transport funds. Assessments will be administered by research assistants blinded to study arm. For peer leaders who are no longer employed by the study, we will be flexible in the location (remote or in-person) of data collection. All peer leader data will be de-identified prior to review by investigators and the study coordinator to preserve confidentiality and eliminate fear of recrimination, except if they endorse severe distress, in which case they will be evaluated and referred (as needed) for care.

#### Demographics

Peer leaders will report their age, marital status, number of children, education, food security, and stable housing.

#### Primary outcome

The percentage of peer leaders retained at 6-months.

#### Secondary outcomes

The percentage of peer leaders retained at 12-months; Job satisfaction [68] at 6- and 12-month follow-up.

**Mediators and moderators**: At baseline, pre-workshop day 1, and 6- and 12-month follow-up, peer leaders will report their confidence delivering sex education (*Sex Education Confidence Scale* (SECS)) [69], HIV and STI knowledge [51], job satisfaction (*Satisfaction of Employees in Health Care (SEHC))* [70], PrEP knowledge and attitudes [52], depression (Patient Health Questionnaire-9 [58]), anxiety (GAD–7 [71]), trauma (PC-PTSD-5 [72]), alcohol use (AUDIT C [63], and drug use (ASSIST 3 [62]). Peer leaders who screen positive for clinically significant distress (GAD-7: ≥ 10; PHQ-9: ≥ 10; PC-PTSD5 ≥ 3) or alcohol and substance use disorder (AUDIT C: ≥ 3; ASSIST3 ≥ 4) at any assessment will be referred for further evaluation and treatment at the closest government facility. If peer leaders report suicidal ideation, they will be immediately referred to counseling.

### Aim 4 ZAIMARA implementation outcomes

**Overview**. We will use a combination of surveys, source documentation, focus groups, and individual interviews to evaluate the acceptability, appropriateness, feasibility, fidelity, sustainability, and costs associated with ZAIMARA.

**Participants**. Participants will comprise six different groups representing each clinic site in the study: AGYW (*n* = 15), MF (*n* = 15), peer leaders (*n* = 10), research staff (*n* = 10) (i.e., local investigators, study coordinator, research nurses, research assistants, data manager, M&E coordinator), clinic personnel (*n* = 10) (i.e., nurses providing HIV and/or STI or other health services to adolescents, department heads), and other key partners (*n* = 15) (i.e., Ministry of Health, Technical Working Group, community leaders, religious leaders, local councilors, and Community Based Organization representatives). To be eligible, AGYW and MF must have participated in the effectiveness trial and the 24-month follow-up. For all others, a willingness to consent is required. All participants must have knowledge of ZAIMARA, its goals and objectives, and its procedures.

**Recruitment.** We will invite research staff and clinic personnel at all five sites to complete implementation surveys before workshop day 1 and again at 6-, 12-, and 24-month follow-ups. We will invite peer leaders who deliver ZAIMARA, research staff and clinic personnel, and key partners to participate in separate focus group discussions (FGDs) at the completion of the study. We will invite select partners, AGYW, and MF to participate in individual in-depth interviews (IDIs) remotely or in person. Participants will complete informed consent prior to data collection. The consent process will emphasize that study engagement is voluntary and will have no impact on their employment or the ability to receive services at the site. Exceptions to confidentiality as required by law will be explained.

**Procedures.** We will use a combination of self-report, monitoring logs, attendance records, clinical information, and structured observations to assess ZAIMARA’s implementation. FGDs (60–90 min) and IDIs (45–60 min) will be conducted at the end of the study by an experienced qualitative researcher in a quiet, private space in the participant’s preferred language (national or local) and using a semi-structured guide. IDIs and FGDs will be audio-recorded, and field notes will be taken during the interviews to characterize non-verbal cues, body language, and context. Using Proctor’s Implementation Outcomes Framework [73], we will conduct a qualitative investigation of ZAIMARA’s acceptability, appropriateness, fidelity, feasibility, sustainability, and cost effectiveness to improve future integration and intervention uptake [73–75]. The qualitative research assistants will maintain audio-recordings, notes, and analytical memos. We will provide a transport refund of K200 (~$9.00) to all participants. Table 2 indicates the implementation measures, theoretical framework, data source, and the time points for data collection.

**Table 2 Tab2:** Implementation research measures, timepoints, source material

Topic	Items	Timepoint(s)	Source material
Reach	3	Completion of enrolment	Neighborhood Health Committee Members, Research Staff, Peer Leaders
Reach	1	Completion of enrolment	% of eligible AGYW enrolled in ZAIMARA. Catchment area estimates and enrolment numbers
Adoption	13	Pre-workshop day 1; 6-mo; 12-mo	Peer leaders
Adoption	13	Pre-workshop day 1; 6-mo; 12-mo; 24-mo	Clinic personnel; Research staff
Adoption	1	Study completion	% of sites and MoH staff intending to adopt ZAIMARA
Implementation	3	Pre-workshop day in the site 1; 6-mo	Peer leaders
Maintenance	16	Pre-workshop day in the site 1; 6-mo; 12-mo; 24-mo	Clinic personnel; Research staff; Community sensitization
Maintenance	16	Pre-workshop day 1; 6-mo; 12-mo	Peer leaders
Feasibility	6	6-mo	Peer leaders
Feasibility	9	Workshop day 2	AGYW, MF
Acceptability	5	6-mo	Peer leaders
Acceptability	6	Workshop day 1 and 2	AGYW, MF
Appropriateness	6	Workshop day 2	AGYW, MF
Appropriateness	6	6-mo	Peer leaders; Research staff; Clinic personnel
Fidelity	17	Workshop day 1 and 2; 25% reliability check	Peer leader observers; Local trainers
Sustainability	9	12-mo, 24-mo	Research staff
Cost effectiveness	NA	Study completion	Study records, expenditures, spread sheet

### Data analyses

**Overview.** We will use a mixed-methods convergent parallel design to explore the effectiveness of ZAIMARA in increasing HIV testing in 15-19-year-old AGYW, and the implementation reach, adoption, appropriateness, acceptability, feasibility, fidelity, maintenance, evaluation, and cost-effectiveness. We will analyze qualitative and quantitative data separately, place findings side by side on a results matrix to triangulate findings and examine how they converge/diverge and relate to each other to determine the completeness and strength of the evidence.

**Missing data**. We expect missing data to result from subject attrition. We expect at least 80% retention at 6-months (the primary outcome point) based on prior research. We will examine if AGYW who complete the follow-up assessments differ systematically on baseline data from those lost to follow-up. In the absence of evidence to the contrary, missing values will be regarded as missing at random (a function of observed outcomes and covariates), and we will use all available data (including non-completers) in analyses. We will conduct a sensitivity analysis to quantify potential bias due to non-ignorable dropout.

## Data management

All participants will be assigned a unique identification number. Survey data will be collected using REDCap (Research Electronic Data Capture), a web-based platform [76, 77], and stored in password-protected cloud-based system and secure server maintained at the Centre for Infectious Diseases Research in Zambia (CIDRZ). A research nurse at each site will collect laboratory data and record results in a REDCap file separate from personal identifiers and survey data. Data will be accessible only to study personnel. [name] (MPI) and [name] (MPI) will review requests to access the data, and data files will be de-identified prior to sharing with others. Study investigators will check for data completeness and accuracy, and the confidentiality of records will be upheld.

